#### Safety index

Safety indices will be routinely assessed using blood, urine, and stool samples and by performing liver and renal function tests. These will be measured at baseline and the eighth week after enrollment.

### Data collection and management

If participants deviate from the intervention program, additional participants will be included to minimize data loss during the study period. Patients will be supervised and guided by specialized researchers throughout the intervention. At the fourth and eighth weeks, participants will be required to return to the hospital for scale (Such as clinical symptoms, SAQ and TCM syndrome scores) or clinical-related tests, and regular telephonic follow-up will be conducted by researchers during the follow-up period. Researchers remind patients to undergo daily moderate-intensity training, and those who deviate from the intervention plan will receive telephonic reminders, to ensure the integrity of the study data.

Basic patient information and relevant information required for the study will be recorded in the printed case report form (p-CRF). The patient's medical records (medical records, test sheets, etc.) will be stored in the hospital, and the doctor records the patient's test results in the observation medical records. Only authorized researchers, ethics committee members, and relevant research management department members will be able to access patient records following reasonable request. The name and identity of the patient will not appear in the study and published papers. The research team will do everything possible to protect the privacy of patients' personal medical data from disclosure within the scope permitted by law.

### Quality control

Quality control will be conducted throughout the test. Before the start of the trial, all researchers will receive unified clinical trial training to fully understand the trial scheme, trial process, and shared tasks. For example, the Independent Data and Safety Monitoring Committee (DSMB), composed of two cardiologists and a statistician, will closely monitor the participants' trial data; to prevent data loss, researchers will be responsible for reminding participants to complete the exercise. In addition, investigators will receive unified training, including in regard to data management and filling out of the p-CRF to ensure high-quality completion of the trial.

### Statistical analysis

A full-analysis set (FAS), per-protocol analysis set (PPS), and safety analysis set (SAS) will be created according to the principle of intentional therapy (34). FAS participants are identified as those who received at least one exercise. Those who adhere to the treatment plan but changed groups midway are part of the PPS. For safety indicator assessment, researchers will use the SAS to analyze the incidence of adverse events and laboratory indicators. Statistical analysis will be conducted by third-party statisticians blinded to experimental grouping and intervention methods, using SPSS 25. We will analyze the baseline demographic data to determine the comparability between the two groups. Mean ± standard deviation will be used for continuous variables that conform to normal distribution, and median and quartile methods will be used for continuous variables that do not conform to normal distribution. The Chi-square test or Fisher's exact test will be used to compare classified counting data. The paired *t*-test will be used to compare differences within the group, and the independent-sample *t*-test will be used to compare differences between groups. If the data do not conform to normal distribution, a Wilcoxon paired test and Mann-Whitney U test will be used to analyze intra- or inter-group differences. *P* < 0.05 is considered as statistically significant.

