#### Criteria for withdrawal and removal

(1) Researchers will further exclude the following patients:① Those who were not suitable to continue with the trial;② Those with poor compliance, which affects their judgment of efficacy and safety;③ Those with disease progression to acute coronary syndrome;④ Those unable to perform Baduanjin exercises due to serious musculoskeletal problems.(2) Self-withdrawal is characterized as follows:① Unwillingness or inability to continue with the clinical trial for any reason;② Not explicitly intending to withdraw from the trial but no longer being treated and tested.

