### Sample size

The sample size was calculated according to the effective rate of the Baduanjin group and the control group. Referring to the previous research (27), it is assumed that the effective rate of the combination of traditional Chinese medicine and western medicine is 76.2%, and the effective rate of western medicine is 45.8%. Based on the class I error rate of α = 0.05 and the efficacy of 90% (II error rate of β = 0.1), bilateral test, and considering the shedding of 20%, the experiment was expanded to 69 people. Because the reference study is drug intervention, considering that this study is non-drug intervention, we continue to expand the sample size to 90 people in each group, a total of 180 people.

$$\begin{array}{l} n=\frac{{\left(u_{\alpha }+u_{\beta }\right)}^{2}\left(1+1/k\right)p\left(1-p\right)}{{\left(p_{e-}p_{c}\right)}^{2}} \end{array}$$

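### The per-protocol set is worded to admit patients who changed groups, which reverses its purpose; the damage is confined to that supportive analysis

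*Protocol article*

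**What the plan says.** The protocol article's Statistical analysis section sets up three analysis sets: full analysis, per protocol and safety. It says that they "will be created according to the principle of intentional therapy", evidently meaning intention to treat. The FAS has an entry rule: "FAS participants are identified as those who received at least one exercise". The PPS has one membership sentence: "Those who adhere to the treatment plan but changed groups midway are part of the PPS". No other part of the article restates, qualifies or corrects it. The article does not name the PPS as the set for the primary analysis.

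Two other sections bear on compliance. Criteria for withdrawal and removal lists among those to be excluded: "Those with poor compliance, which affects their judgment of efficacy and safety". Data collection and management says: "If participants deviate from the intervention program, additional participants will be included to minimize data loss during the study period".

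**The concern.** A per-protocol set exists to show the effect among patients who did what their allocation asked of them. Moving to the other arm is about as clear a departure from allocation as this trial allows, yet the sentence lets such patients in. The two halves of the rule cannot both be satisfied in the usual sense of adherence.

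If the rule were programmed as printed, the PPS would contain people who had done some of each intervention, and there are two ways to count them:

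- **As allocated.** Each arm then holds some people exposed to the other arm's exercise, so the difference is pulled towards zero.
- **As received.** Membership of an arm then depends partly on who chose to move and why, so the comparison is confounded by whatever drove the switch.

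In either case the PPS does less well the one job it has, which is to stand beside the FAS as a supportive analysis.

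**Working it through.** **1. The text set side by side.** Compliance matters elsewhere in the plan: poor compliers may be removed because they cloud the judgement of efficacy and safety, and deviation from the programme leads to extra recruitment. The PPS sentence goes the other way and keeps a clear class of deviators in the set meant to be cleanest. Nothing in the article reconciles the two.

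**2. The plan's own sample size.** The inputs are from the Sample size section: rates 76.2% and 45.8%, two-sided α = 0.05, power 90%, k = 1, 20% loss.

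- Mean rate p = (0.762 + 0.458)/2 = 0.61.
- n = (1.960 + 1.282)² × 2 × 0.61 × 0.39 / 0.304² = 54.1, rounded up to 55.
- 55/0.8 = 68.75, rounded up to 69, which is the stated figure. The plan then raises it to 90 per group.

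The plan's number therefore reproduces, and nothing numerical is wrong on this point.

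**3. Illustration of dilution.** The documents give no switching rate, so every value of x below is an assumption. Three more are made: a fraction x of each arm switches; switchers take on the other arm's full rate but are counted in their allocated arm; and 72 per arm remain (90 × 0.8).

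- Rates become 0.762 − 0.304x and 0.458 + 0.304x.
- Difference d = 0.304 × (1 − 2x). The mean rate stays at 0.61.
- Power = Φ{[d√72 − 1.96√(2 × 0.61 × 0.39)] / √(p₁(1 − p₁) + p₂(1 − p₂))}.
- For x = 0: (0.304 × 8.485 − 1.96 × 0.690)/0.655 = 1.87, so power is 96.9%.

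| Switching each way | Rates | Difference (points) | Power at 72 per arm |
|---|---|---|---|
| 0% | 76.2% v 45.8% | 30.4 | 96.9% |
| 5% | 74.7% v 47.3% | 27.4 | 92.8% |
| 10% | 73.2% v 48.8% | 24.3 | 85.7% |
| 15% | 71.6% v 50.4% | 21.3 | 75.0% |

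**4. Switching partway.** The sentence speaks of a change during the intervention, not from its start. If half the exposure carries half the effect (a further assumption), d = 0.304 × (1 − x). Then 10% switching gives 27.4 points, the same as 5% switching for the whole period. The table is therefore towards the pessimistic end for any given x.

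**The case against.** The strongest reply is that this is a slip of language. The sentence is self-contradictory as printed, and the same paragraph misnames intention to treat, so a lost 'not' is more likely than a deliberate choice. That is probably right. It explains the error but does not remove it: this is the only published PPS rule, and the analysts should not have to guess what was meant.

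The second reply is that switching may be rare. Baduanjin is a taught sequence, its participants are told not to do other exercise, both arms are supervised, and those who deviate are reminded by telephone. This stands as a limit on size, and it is why the illustration starts at zero. The illustration's other inputs are also open to challenge: the two rates come from a drug study that the article itself says differs from this intervention, and 72 per arm applies the 20% loss to 90, whereas the plan applied it to reach 69.

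Three stronger readings are tempting and not supported:

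- **That the PPS consists of switchers only.** The sentence says that they belong to the set, not that they make it up.
- **That agreement between FAS and PPS would be meaningless.** With few switchers, a set limited mainly to adherers still differs from one that needs only a single exercise session.
- **That counting switchers as received uniquely breaks randomisation.** Every per-protocol subset conditions on events after randomisation. Counting as received adds a further layer of self-selection.

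**Conclusion.** The sentence is wrong as written and should be fixed. It is a stated rule that contradicts itself and inverts the set it defines, not detail that an article leaves to an analysis plan.

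The harm is limited to the supportive PPS analysis. A reader might infer that the main result is compromised. The documents do not support that: the PPS is not named as primary, and an FAS analysis by allocated group does not use this rule. A reader might also infer a power shortfall, but the trial was not sized on the PPS, so a lower PPS power breaches no stated target. With switchers counted as allocated, the pull is towards no difference.

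The size depends wholly on how many patients switch and when, which the documents do not say. It runs from nothing at 0% to a loss of about 9 points (30.4 to 21.3) at 15% switching each way for the whole intervention, with less if the switch is partial.

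**What to change.** Correct the one sentence so that the PPS contains FAS participants who adhered to their allocated intervention and did not change groups. State that group changers stay in the FAS and are analysed as randomised. Since the Trial status section says that recruitment has begun, make the correction before the data are analysed, so that the rule cannot appear to have been chosen in the light of results.

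The cost is a slightly smaller PPS. Sample size, α and trial conduct do not change. A session threshold or required visits for PPS entry can be left to the analysis plan, since the error in this sentence does not turn on them.

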### Outcome measurements

Table 1 provides a detailed overview of the items that will be measured for the primary and secondary results, and the time of data collection. The main outcome indicators will be measured prior to the experiment (week 0), after the end of the trial (week 8), and at 3 and 6 months after enrollment. Data on the secondary outcome indicators, including the duration of angina pectoris, number of angina pectoris weeks, nitroglycerin consumption, nitroglycerin reduction rate, SAQ, quality of life (SF-36), and TCM syndrome scores, will be collected at weeks 0, 4, and 8 and months 3 and 6. Details on secondary outcome indicators, including electrocardiogram (ECG) readings, blood lipid and hs-CRP levels, and intestinal microflora, will be collected during weeks 0 and 8. All measured outcomes will be recorded in the case report form.

**Table 1 T1:** Schedule of trial measurements for primary and secondary outcomes.

**Study phase**		**Screen/enroll**	**Allocation**	**Intervention period**	**Intervention end**	**Follow-up period**	**Follow-up period**
**Time points**		**Week 0**		**Week 4**		**Month 3**	**Month 6**
Screening/enrollment	Eligibility screening	•	•	—	—	—	—
	Informed consent	•	—	—	—	—	—
	Baseline measurement	•	—	—	—	—	—
	Random allocation	—	•	—	—	—	—
Intervention	Baduanjin exercise	—	•				•
	Free activities	—	•				•
Outcome assessment	Total effective rate	—	•	•	•	•	•
	Duration	—	•	•	•	•	•
	Attack frequency	—	•	•	•	•	•
	Dosage	—	•	•	•	•	•
	Stopping rate of nitroglycerin	—	•	•	•	•	•
	SAQ	—	•	•	•	•	•
	SF-36	—	•	•	•	•	•
	ECG	—	•	—	•	—	—
	Serum lipids	—	•	—	•	—	—
	Hs-CRP	—	•	—	•	—	—
	The TCM syndrome scores	—	•	•	•	•	•
	Composition of gut microbiota	—	•	—	•	—	—
	TMAO	—	•	—	•	—	—
Safety index	—	—	•	—	•	—	—
Adverse events	—	—	•				•

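### Continuous secondary outcomes are compared between groups without using their baseline values: the tests are valid but less precise than ANCOVA, and the paired within-group tests should be descriptive only

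*Protocol article*

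**What the plan says.** The Statistical analysis section of the protocol article names its tests by type of data:

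- Continuous outcomes: "the independent-sample *t*-test will be used to compare differences between groups", with a paired t-test inside each arm named in the same sentence.
- Non-normal data: "a Wilcoxon paired test and Mann-Whitney U test will be used to analyze intra- or inter-group differences".
- Categorical data: chi-square or Fisher's "exact test will be used to compare classified counting data".

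No covariate or model is named. The only stated use of baseline data is a check that the arms are demographically comparable. One threshold, P < 0.05, covers all tests.

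The baseline values are nevertheless scheduled. Under Outcome measurements, the symptom measures, SAQ, SF-36 and TCM score "will be collected at weeks 0, 4, and 8 and months 3 and 6". ECG, lipids, hs-CRP and flora are taken at weeks 0 and 8. The metabolomics item under Secondary outcome puts the TMAO blood samples at the same two times.

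The primary outcome is a responder rate. Its index is the percentage reduction from the pre-trial symptom score, with response starting at 30% (Table 3 and its description).

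**The concern.** A baseline measure of the same quantity is usually the best available predictor of the follow-up value. A test on follow-up values alone leaves that information unused. A test on changes uses it with a fixed slope of 1, which is generally not the best weight. In either case the group difference is estimated with a wider interval than the collected data allow. The secondary outcomes carry the quality-of-life and mechanistic aims, and the sample size was set on the responder rate, not on them.

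The paired tests raise a separate issue. Both arms receive basic treatment, health education and supervised exercise 3 to 5 times a week (Baduanjin group and Control group sections), so both may change. A P-value below 0.05 in one arm and above it in the other says little about the difference between arms, which is the trial's question.

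**Working it through.** **1. The plan's own sample size, to settle where the primary stands.** Inputs from the Sample size section: "class I error rate of α = 0.05"; "the efficacy of 90% (II error rate of β = 0.1), bilateral test"; effective rates 76.2% and 45.8%; 1:1 allocation.

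The printed formula with k = 1 and p = (0.762 + 0.458)/2 = 0.61 gives

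n = (1.960 + 1.282)² × 2 × 0.61 × 0.39 / 0.304² = 54.1, rounded up to 55 per group.

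With 20% dropout, 55/0.80 = 68.75, so 69. This reproduces the stated "considering the shedding of 20%, the experiment was expanded to 69 people", read as a per-group figure. The plan then goes to 90 per group, which leaves 90 × 0.80 = 72 evaluable.

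Power at 72 per group and the plan's own rates:

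Φ{[0.304 × √72 − 1.960 × √(2 × 0.61 × 0.39)] / √(0.762 × 0.238 + 0.458 × 0.542)} = Φ{(2.580 − 1.352)/0.655} = Φ(1.87), about 96.9%.

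The same formula gives 99.0% with 90 per group.

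**2. Continuous outcomes.** Let r be the correlation between baseline and follow-up within an arm. The documents do not give it; 0.3 to 0.7 is an assumed range. With equal variances at the two times and a linear relation, the variance of the group difference, relative to a t-test on follow-up values, is:

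- change-score t-test: 2(1 − r)
- ANCOVA: 1 − r²
- hence ANCOVA relative to change score: (1 − r²)/[2(1 − r)] = (1 + r)/2

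| Assumed r | Change / follow-up | ANCOVA / follow-up | ANCOVA / change |
|---|---|---|---|
| 0.3 | 1.40 | 0.91 | 0.65 |
| 0.5 | 1.00 | 0.75 | 0.75 |
| 0.7 | 0.60 | 0.51 | 0.85 |

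For any r strictly between 0 and 1, both ANCOVA ratios are below 1. At r = 0.5 the gain equals 1/0.75 = 1.33, or about 33% more patients. For an effect that the follow-up t-test detects with 80% power, the powers at r = 0.3, 0.5 and 0.7 are:

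- ANCOVA: 84%, 90% and 98%
- change-score test: 66%, 80% and 95%

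**3. Paired tests within arms.** Suppose both arms truly change by the same standardised amount d (mean change over SD of change), with 72 per arm. Each paired test is significant with probability about p = Φ(d√72 − 1.96) + Φ(−d√72 − 1.96). Exactly one of the two arms is significant with probability 2p(1 − p):

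| Assumed d | p | Exactly one arm significant |
|---|---|---|
| 0.1 | 0.136 | 0.235 |
| 0.2 | 0.396 | 0.48 |
| 0.3 | 0.721 | 0.40 |

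The maximum is 0.50, at p = 0.5. So a change significant in one arm only is common even when the arms do not differ.

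**4. Adjusting the primary.** Chi-square was compared by simulation with logistic regression on one baseline covariate, with 72 per arm and an assumed smaller effect of 64.8% against 45.8% (1,500 runs per setting). Chi-square power was 63 to 65%. Adjusted power was 64 to 65% when the covariate's log odds ratio per SD was 0 to 0.5, which is no gain, and 70% when it was 1.0, a gain of about 7 points. The documents do not report how strongly baseline predicts response.

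**The case against.** The strongest reply is that nothing here is wrong. With 1:1 randomisation, the unadjusted tests control the type I error, and chance baseline imbalance is already reflected in the standard error. That stands: the point concerns precision, not bias.

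The second reply is that the precision figures have limits. They assume r, and they hold for approximately continuous outcomes with a linear relation. They do not carry over to a Mann-Whitney test, or to weekly attack and tablet counts that may contain many zeros. That also stands, and it restricts the quantified claim to outcomes such as SAQ, SF-36, TCM score, lipids, hs-CRP and TMAO, the skewed ones after log transformation.

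A reader might also infer more than the article supports:

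- *That every outcome would gain.* The responder rate and the nitroglycerin and ECG grades are already defined against the pre-treatment state.
- *That patients with a missing visit will be dropped in visit-by-visit tests.* The article does not say how visits or missing values are handled, and it may leave this to the analysis plan.
- *That both arms are bound to improve by regression to the mean.* The inclusion criteria set no minimum symptom score or attack frequency, so this is possible but not established.
- *That within-group P-values will be presented as efficacy.* The article pairs them with between-group tests and nowhere says so. The risk lies in interpretation.

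What remains is that the article itself states the tests, without a covariate, so this is a choice it has made and not a detail left open.

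**Conclusion.** The point holds as an efficiency recommendation for the continuous secondary outcomes. ANCOVA would have 0.91 to 0.51 of the variance of a follow-up t-test and 0.65 to 0.85 of that of a change-score t-test, for assumed correlations of 0.3 to 0.7. It improves on both, so the conclusion does not depend on which one the article means; only the size of the gain does.

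The primary analysis is not endangered at the planned effect. Baseline adjustment there is optional, with a gain from none to modest that depends on a prognostic strength the documents do not give.

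The paired tests can stay as description but cannot support a statement about the difference between arms.

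**What to change.** In the Statistical analysis section or the analysis plan, before unblinded data are seen:

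1. For approximately continuous outcomes measured at weeks 0 and 8 (lipids, hs-CRP, TMAO), make the between-group comparison an ANCOVA on the baseline value, log-transformed if skewed. Report the adjusted difference with its 95% confidence interval.
2. For scales with repeated visits (SAQ, SF-36, TCM score), use the same ANCOVA at a named visit, or a mixed model with arm, visit, arm by visit and baseline value.
3. For weekly attack counts and nitroglycerin tablets, use a method suited to counts, also adjusted for the baseline value.
4. Label the paired t- and Wilcoxon tests descriptive, and state that conclusions on effect rest on between-group comparisons only.
5. Optionally, adjust the responder rate for baseline symptom score and report a standardised risk difference. A plain logistic model would change the effect measure to a conditional odds ratio.

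The cost is a few sentences of analysis wording and slightly more analysis work. No new data, visits or patients are needed.

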### Safety assessment

The safety index is used to evaluate the security of this study. If adverse events (such as disability, death, etc.) occur during the study, researchers will assess the relationship between the event and intervention and report it to the Ethics Committee and DSMB to determine whether those participants should withdraw from the trial. During the study period, any study-related damage will be treated accordingly, following identification by the Beijing Medical Accident Identification Committee, and followed up until recovery or until the patient became stabilized, with the expenses covered by Guang'anmen Hospital.

## Discussion

This experiment will evaluate the efficacy and safety of Baduanjin in patients with SAP and detect changes in intestinal flora and the metabolite TMAO.

Angina pectoris is a cardiovascular disease characterized by chest pain. Clinically, it is divided into SAP and unstable angina pectoris (35). SAP is the most common symptom of coronary heart disease. Although the overall prognosis is good, the annual incidence of events is 1–2% (36). For many people, its symptoms seriously affect their lifestyle. In severe cases, it can develop into myocardial infarction. As a traditional Chinese Qigong, Baduanjin has been used in health care for a long time. Its movements are simple and unrestricted by location (15). Studies have shown that Baduanjin can effectively improve cardiac function (17).

Additionally, the occurrence of SAP is reportedly related to changes in intestinal microflora (37). Exercise can increase the concentration of short-chain fatty acids in feces and the ability of intestinal microflora to produce short-chain fatty acids (38). Therefore, we hypothesize that Baduanjin may be related to the function of intestinal microflora. Further, we explored the mechanism of its effect on SAP based on the composition of intestinal microflora. If successful, the trial will provide SAP patients with a good exercise program and encourage them to improve their quality of life by using Baduanjin as an adjuvant treatment.

Our experiment had several advantages: we used a strict randomized control method, which was strictly confidential to evaluators and statistical analysts, thus enhancing the reliability of the experiment; Baduanjin, as a traditional Chinese method, is a trustworthy method (having been around for years) and is easy to perform, thus increasing compliance; and Baduanjin is simple and gentle and is very easy for patients with SAP to perform. In addition, if the experiment proves to be effective, Baduanjin not only improves the quality of life of patients, but also reduces medical expenses and saves medical resources.

There were two main limitations in our experiment: it was a single-center experiment; therefore, it is smaller than multi-center experiments. It is not clear whether the Baduanjin exercise works in other patient ethnicities. In addition, it is not clear if the participants will receive additional training on this technique as it requires constant supervision and visits by researchers.

In conclusion, this experiment will confirm whether Baduanjin can be used as an adjuvant therapy for SAP. This randomized controlled trial will help to provide evidence to verify whether the mechanism of Baduanjin improving SAP is related to gut microflora.

